# Application effect of extensively hydrolyzed milk protein formula and follow-up in preterm children with a gestational age of less than 34 weeks: study protocol for a randomized controlled trial

**DOI:** 10.1186/s13063-015-1030-5

**Published:** 2015-11-04

**Keywords:** Extensively hydrolyzed formula, Preterm children, Feeding intolerance, Growth and development, Follow-up

## Abstract

**Background:**

The average incidence of preterm birth in the world is up to 11.1 %, and deaths of preterm children account for more than 50 % of neonatal deaths. Gastrointestinal function of preterm children with a gestational age less than 34 weeks is immaturely developed. For preterm children who can only be fed with formula due to their mothers’ sickness, choosing a suitable formula can not only meet the high nutritional needs of preterm children, but also solve their low gastrointestinal tolerability, and is thus very important.

**Methods/Design:**

The study is a prospective, randomized, single-blind and controlled clinical trial. Preterm children with a gestational age less than 34 weeks meeting the inclusion criteria who cannot be breastfed will be included. To demonstrate the application effect of extensively hydrolyzed milk protein formula on the target population, preterm children will be randomized into two groups, 185 subjects in each group. The observation group will be fed with extensively hydrolyzed milk protein (100 % whey protein) formula, while the control group will be fed with preterm children’s formula until the children are discharged from the neonatal intensive care unit (NICU). All the formula involved in this study will be from Dumex. After discharge, both groups will be uniformly fed with formula for 0 to 6-month-old infants. For statistical analysis, a chi-square test and Student’s *t* test will be applied using SAS 9.4.

**Discussion:**

This will be the first randomized controlled clinical study with long-term observation of the growth and development of preterm children during the NICU stay and at 3-month follow-up after discharge from the NICU. Results from this study will be used to determine whether the extensively hydrolyzed formula is more suitable for the low gastrointestinal tolerability of preterm children, and also whether feeding preterm children who are fed with such formula during the NICU stay with ordinary infant formula after discharge from the NICU would affect the normal growth and development of preterm children in the early stage of their lives.

**Trial registration:**

This study was registered with the Chinese Clinical Trial Registry (http://www.chictr.org.cn/) with number ChiCTR-IOR-14005696, on December 22, 2014.

## Background

The neonatal period is a special period of life, in which the infant gradually transforms from complete dependence on the mother for survival into a mature individual. In 1976, the World Health Organization (WHO) defined preterm children as newborns with a gestational age of <37 weeks (<259 days) [1]. In 2005, the American Academy of Pediatrics and the American College of Obstetricians and Gynecologists [2] defined newborns with a gestational age of 34–36^+6^ weeks as late preterm birth, and less than 34 weeks as early preterm birth; in 2012, the WHO [3] defined preterm children with a gestational age of <28 weeks as extremely preterm birth, 28–31^+6^ weeks as very preterm birth, 32–36^+6^ weeks as moderate preterm birth, and 34–36^+6^ weeks as late preterm birth. The incidence of preterm birth varies greatly in different countries. In 2010, the incidence of preterm birth in 11 countries worldwide was ≥15 % [4]. The average incidence of preterm birth all over the world is up to 11.1 %. A total of 14.9 million preterm children are born worldwide every year [5], and in these preterm live births, more than 1 million preterm children eventually die [6], accounting for more than 50 % of neonatal deaths. In China, there is little data on the incidence of preterm birth nationwide. The WHO reported that the incidence of preterm birth in China in 2010 was <10 % [4]. The number of preterm children in ten countries including China accounts for 60 % of the world’s total. The mortality of preterm children in China is very high. From 2000 to 2008, preterm children led to 14–15 % of deaths of children younger than 5 years old in China [7]. The younger the gestational age, the lower the birth weight is and the higher the mortality is. According to the above data, we find that in all medical problems of newborns, the improvement of the survival rate and quality of life of preterm children is the target that the world focuses on tackling.

**Fig. 1 Fig1:**
[figure not shown]
CONSORT flowchart of subject enrollment

The fetus in utero obtains nutrition through the placenta as a parenteral nutrition (PN) pathway. After birth, the newborns need to switch to enteral nutrition, while the completion of enteral nutrition requires effective and coordinated sucking-swallowing, gastric emptying, intestinal peristalsis and the digestion and absorption of nutrients. However, these functions of preterm children are immature, and the younger the gestational age, the more immature these functions. First, the increase in the extensibility and absorption area (microvilli) of the gastrointestinal tract of preterm children is mainly completed in the last 3 months of pregnancy [8]. Second, the sucking-swallowing-breathing action of preterm children with a gestational age of less than 32 weeks is much more uncoordinated; only children with a gestational age of 34–35 weeks have coordinated nutritive sucking [9]. In addition, the gastrointestinal motility of preterm children is weak, and the duodenum of preterm children with a gestational age of <32 weeks lacks the spread of migrating motor complex (MMC) [10]. Until after the gestational age of 34 weeks, clear and ever-increasing MMC gradually emerge. The above mechanisms lead to prolonged gastric emptying time and intestinal transit time of food in preterm children, and thus preterm children with a gestational age of less than 34 weeks are prone to gastroesophageal reflux, feeding intolerance (FI), delayed meconium drainage, intestinal dilatation and other phenomena. In addition, the development of digestive enzymes in preterm children is also very immature, and preterm children have inadequate secretion and low activity of gastric acid, gastric protease-pepsin and pancreatic protease, which weaken the ability of the gastrointestinal tract to hydrolyze protein into peptides and amino acids [10]; the concentration of pancreatic lipases and duodenal bile acids is very low [11], which reduces the intestinal absorption of lipids, especially the long-chain fatty acids (LCT). Therefore, preterm children are also prone to extrauterine growth retardation (EUGR) caused by inadequate absorption of enteral nutrition. Currently, a large number of studies have shown that extrauterine growth retardation has definite influences on the subsequent cognition and mental development of preterm children [12].

Nutritional support in the neonatal period is one of the basic conditions for survival of preterm children. Preterm children born in advance for various reasons need parenteml nutrition if enteral nutrition cannot meet their needs for growth and development. Although parenteral nutrition supplement can meet the temporary nutritional needs of preterm children, long-term parenteral nutrition has brought a series of problems, such as difficulties in peripheral venous puncture, susceptibility to complication by infections after central venous catheterization, parenteral nutrition-associated cholestasis (PNAC) and other complications. The ultimate goal of nutritional support in preterm children is to not only reach the normal growth speed of normal fetuses of similar gestational age in utero, but also have similar composition and function to normal fetuses. The ideal growth rate of preterm/low-birth-weight children during the neonatal intensive care unit (NICU) stay, by referring to the growth rate of normal fetuses in utero [13], is required as follows: average daily weight gain of 15 g/kg, weekly body length growth of 1 cm and weekly head circumference growth of 0.5–1 cm. However, preterm children after birth are faced with respiratory, digestive and other problems. For preterm children with various immaturely developed systems, how to solve the conflict between the high nutritional demands and low gastrointestinal tolerability of preterm children is a very realistic and important issue. Therefore, we need an appropriate early enteral nutrition management strategy for preterm children, although there is already a lot of consensus [14, 15], such as breastfeeding, initiation of microfeeding as early as possible, achieving full enteral nutrition as soon as possible, and shortening the time of parenteral nutrition in order to reduce complications. It is preferred to feed preterm children with their mothers’ breast milk [14], because such feeding can reduce the incidence of feeding intolerance, neonatal necrotizing enterocolitis (NEC), nosocomial infections, and growth and developmental retardation in preterm children [16]. In the event of inadequate supply of breast milk due to various reasons or inability of breastfeeding due to maternal diseases, breast milk provided by qualified breast milk donors becomes the second-best nutritional source for preterm children [17] During October 2010 to December 212, a multicenter double-blind controlled study conducted in Canada [18] found that the breast milk of donors was equally safe and effective as the breast milk of preterm children’s mothers, and after long-term follow-up and study, found that donor breastfeeding was favorable for the development of the nervous system in preterm children. In Taiwan, China [19], the breast milk in the breast milk bank is mainly used for feeding preterm children, infants with feeding intolerance and other infants suffering from metabolic disorders. Currently, many developed countries have established large breast milk banks, and breast milk can be shared even via the Internet [20]. However, the breast milk in breast milk banks is mostly for full-term children, whose nutritional ingredients cannot meet the needs of growth and development of preterm children. Breast milk banks have not been set up in most areas of China, and no unified standard donor screening, breast milk collection, disinfection, preservation and feeding practices have been established. The rural population accounts for the majority in China. Rural areas and small cities lack the capacity to treat preterm children, so preterm children are often sent to NICU in large cities for hospitalization. Their homes are often far away from the hospital, and China’s NICUs are mostly accompany-free wards, so family members cannot participate in feeding and care. Besides, many mothers cannot breastfeed because of their illness, and thus, preterm children hospitalized in NICUs in China are mostly fed with formula.

In China, preterm children with a gestational age of less than 34 weeks are mostly fed with preterm children’s formula, and such milk powder provides sufficient energy, protein, vitamins and minerals and features a high growth rate in preterm children. However, excessive weight gain in early infancy will increase the risk of metabolic diseases and cardiovascular diseases in adulthood [21, 22]. The probabilities of feeding intolerance and neonatal necrotizing enterocolitis and overall mortality in preterm children fed with preterm children’s formula are significantly higher than in children fed with breast milk or donated breast milk [23–25]. Therefore, choosing a milk powder more suitable for the intestinal function of preterm children with a gestational age of less than 34 weeks is very important.

Hydrolyzed formula is to hydrolyze protein in milk powder to polypeptides, peptides and free amino acids with bio-lyase, heating, ultrafiltration and other special technologies. The American Academy of Pediatrics (AAP) refers to formula whose peptide molecular weight is less than 3000 Da as extensively hydrolyzed formula (EHF) [26]. According to the protein ingredient therein, the formula can be divided into hydrolyzed protein formula, hydrolyzed soy protein formula and hydrolyzed rice protein formula; according to the milk protein ingredient therein, the formula can be divided into hydrolyzed whey protein, hydrolyzed casein, and hydrolyzed whey protein/casein. The low-molecular-weight peptides and small amounts of free amino acids in extensively hydrolyzed milk protein formula have greatly reduced the conformation and sequence of allergen idiotope, and thus the antigenicity is greatly lowered. The milk powder is mainly used for the treatment of cow’s milk protein allergy (CMPA) [27]. Researchers have fed preterm children in their early stage of life with EHF to prevent the occurrence of CMPA [28, 29], but there is no conclusion on whether it is effective.

EHF has cracked milk protein to low-molecular-weight peptides and partial amino acids, favorable for the gastrointestinal tolerability of preterm children. Frati et al. [30] and Staelens et al. [31] found by adopting different methods that the gastric emptying of EHF was significantly faster than the ordinary formula group; Mihatsch et al. [32] used carmine as a fecal marker and found that in preterm children, the gastrointestinal transit time of extensively hydrolyzed formula was 9.8 hours, while that of standard ordinary formula was 19 hours. The main mechanisms that EHF is favorable for the gastrointestinal tolerability of preterm children are summarized as follows: (1) it promotes gastric emptying [30, 31, 33, 34]; (2) it accelerates gastrointestinal transit [32]; (3) it reduces the activity of opioid receptor agonist-milk protein [35]; and (4) it induces motilin (MOT) and gastrin (GAS) secretion [36], thereby reducing the incidence of gastroesophageal reflux (GER) [30, 34, 37], feeding intolerance, etc., in preterm children [38] so as to achieve full enteral nutrition as soon as possible and reduce the time of parenteral intravenous nutrition and a series of complications caused by parenteral nutrition.

Each 100 ml of the EHF used in this study can provide 66 kcal, whose protein-to-energy ratio (P/E) is 2.42 g/100 kcal, lower than the P/E recommended by the European Society for Paediatric Gastroenterology, Hepatology, and Nutrition (ESPGHAN) [39]. Can extensively hydrolyzed milk protein formula meet the high nutritional needs of preterm children? Current study findings have differing conclusions [40–44]. Some studies conclude, by detecting the concentrations of amino acids in serum and urine and intestinal absorption of nitrogen after preterm children are fed with different milk powders, that the protein content in hydrolyzed milk protein formula should be higher than ordinary preterm children’s formula in order to meet the needs of preterm children for growth and development [40–42]. However, these studies all have too small sample size (15 cases, 21 cases, 16 cases), the period of literature [40] study is too short (the conclusion is drawn from determination of plasma amino acid concentrations only after cross feeding with the two kinds of milk powder for 5 days), and in the above studies, the preterm children began to be fed with hydrolyzed formula after achieving full enteral feeding (EF) or 1 week after birth instead of feeding with hydrolyzed formula immediately after birth. Szajewska et al. [43] conducted a randomized controlled study of up to 12 weeks. The authors randomized low-birth-weight children for feeding with different milk powders, then tracked and monitored the growth and development (weight, body length and head circumference growths) and all plasma parameter indicators (urea, albumin (ALB), prealbumin, transferrin, and concentration of each amino acid) of these infants at the beginning of feeding, 4 weeks, 8 weeks and 12 weeks after feeding, and found that the nutrition of extensively hydrolyzed whey protein formula was equivalent to that of the standard preterm children’s formula. In China [44], a multicenter (eight domestic first-class grade 3 hospitals) controlled clinical study from February 2012 to December 2013 found that extensively hydrolyzed milk protein formula could promote the gastrointestinal motility of preterm children and accelerate their metabolism and excretion of bilirubin, without increasing the occurrence of EUGR at discharge. Besides, there is no study at home and abroad on whether feeding preterm children with relatively low-energy low-protein extensively hydrolyzed milk protein formula in the early stage of life will affect their subsequent growth and development. Although studies [28, 29] respectively followed up preterm children and extremely low-birth-weight children after feeding with EHF for the early stage of life for 12 months and 5–7 years, these two studies were conducted only to observe whether EHF could prevent the subsequent occurrence of CMPA in preterm children, without tracking and observing the growth and development of those preterm children.

## Methods/Design

A prospective, randomized, single-center, single-blind and controlled clinical trial will be conducted in preterm children with a gestational age of less than 34 weeks meeting the inclusion criteria who cannot be breastfed. The implementer of the study will be the NICU of Zhongda Hospital Southeast University. The majority of the center’s preterm children are transferred from other hospitals in Nanjing or nearby towns, wherein most preterm children who cannot be breastfed because their mothers suffer from infectious diseases or other severe diseases requiring long-term medication are also transferred to our hospital. Most preterm children hospitalized in our hospital’s NICU can only be fed with formula. Every year, about 2,000 newborns are hospitalized in our hospital’s NICU, and preterm children with a gestational age of less than 34 weeks account for 10–15 % of the inpatients, of whom about two thirds can only be fed with formula.

### Objectives

#### Primary objective

To determine whether feeding preterm children with a gestational age of less than 34 weeks during the NICU stay with extensively hydrolyzed milk protein formula can reduce the rate of food intolerance or not.

#### Secondary objective

To test if the feeding preterm children with a gestational age of less than 34 weeks during the NICU stay with extensively hydrolyzed milk protein formula can accelerate the time to achieve full enteral feeding, shorten the time of parenteral nutrition and NICU stay, benefit spontaneous fecal discharge, reduce the occurrence of other complications associated with parenteral nutrition, and meet the nutritional needs of preterm children during the NICU stay, without affecting the early growth and development of these preterm children during hospitalization and after discharge.

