### Study design and outcomes

#### Outcomes

The first endpoint variable is the rate of food intolerance in preterm children. The second endpoint variables include (1) time to achieve full enteral nutrition; (2) time of parenteral nutrition; (3) time of NICU stay; (4) meconium drainage time; (5) daily spontaneous fecal discharge conditions; (6) growth and development conditions during the NICU stay and within 3 months after discharge, including daily weight growth rate, weekly body length growth rate and weekly head circumference growth rate; (7) different plasma parameter indicators before discharge from the NICU (total protein (TP), albumin, calcium (Ca), phosphorus (P), and alkaline phosphatase (ALP)). Other endpoint variables include the incidences of neonatal necrotizing enterocolitis, cholestasis, parenteral nutrition-associated cholestasis and congenital hypothyroidism (CH).

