### Collection of follow-up data after discharge from the NICU

Weight: weight will be measured once 2 weeks, 4 weeks and 3 months after discharge, respectively, and the data will be accurate to 10 g.Body length: body length will be measured once 2 weeks, 4 weeks and 3 months after discharge, respectively, and the data will be accurate to 0.1 cm.Head circumference: head circumference will be measured once 2 weeks, 4 weeks and 3 months after discharge, respectively, and the data will be accurate to 0.1 cm.

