#### Secondary outcome

The time to reach enteral nutrition (parenteral nutrition), length of hospital stay, meconium drainage time during the NICU stay will be summarized and compared using Kaplan-Meier estimators and logrank tests. Cox models will also be fitted for time-to-event data adjusting for baseline covariates. The number of times of self-defecating per day will be compared using the Poisson model adjusting for baseline covariates. The rates of comorbidity will be compared using Poisson models. The plasma total protein, albumin level, calcium, alkaline phosphatase levels before discharge from the NICU will be compared using *t* tests. Growth rates measure by weight, body length, and head circumference during the NICU and within 3 months of discharge will be analyzed using repeated measurement analysis of covariance models. All analysis will be conducted using SAS 9.4 (SAS Institute, Cary, NC, USA).

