## Discussion

Extensively hydrolyzed milk protein formula can accelerate gastric emptying and gastrointestinal transit time, and promote gastrointestinal hormone secretion, and these mechanisms are conducive for the gastrointestinal tolerability of preterm children, thereby lowering the incidence of gastroesophageal reflux and feeding intolerance in preterm children, achieving full enteral nutrition as soon as possible and reducing the time of parenteral nutrition. In China, more and more medical organizations have started using extensively hydrolyzed milk protein formula to feed preterm children, but so far there is no clear conclusion on whether low-energy low-protein extensively hydrolyzed formula can meet the high nutritional needs of preterm children in the feeding period, and there is a lack of relevant studies and conclusions on whether feeding with extensively hydrolyzed milk protein formula in the early stage of life will affect the subsequent growth and development of preterm children. As the conflict between the high nutritional needs and low gastrointestinal tolerability of preterm children with a gestational age of less than 34 weeks is an unavoidable issue, we have designed this study protocol, aiming to increase a new and truly safe and effective enteral nutritional prescription. Our study observes the effect of extensively hydrolyzed milk formula on the feeding intolerance, enteral and parenteral nutrition, spontaneous fecal discharge and other complications in preterm children with a gestational age of less than 34 weeks during the NICU stay; it also is the first controlled clinical study with long-term observation of the growth and development of preterm children fed with such formula in the early stage of life. Our study time includes NICU stay and 3-month follow-up after discharge of preterm children. The results of this study will confirm that feeding preterm children with such formula during the NICU stay is safe and effective, and does not affect the normal growth and development of preterm children in the early stage of their lives.

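### A no-effect conclusion on growth is stated, but the planned growth analysis has no margin or confidence-interval criterion that could support it

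*Protocol article*

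**What the plan says.** The Secondary objective of the protocol article asks whether EHF feeding brings several benefits and meets nutritional needs "without affecting the early growth and development of these preterm children during hospitalization and after discharge". The Outcomes section lists growth during the NICU stay and up to 3 months after discharge, "including daily weight growth rate, weekly body length growth rate and weekly head circumference growth rate".

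Under Statistical analysis, Secondary outcome, growth rates "during the NICU and within 3 months of discharge will be analyzed using repeated measurement analysis of covariance models". The nutritional blood markers are also tested for a difference: "The plasma total protein, albumin level, calcium, alkaline phosphatase levels before discharge from the NICU will be compared using" *t* tests. The only decision rule in the article is p < 0.05 for a difference, and it is given for the primary outcome alone. The sample size rests on food intolerance alone. No section gives a margin, an equivalence or non-inferiority hypothesis, or a confidence-interval criterion for growth.

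The Discussion closes by saying that the results will establish that the formula is "safe and effective, and does not affect the normal growth and development of preterm children in the early stage of their lives".

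After discharge, visits are counted from the day of discharge: "weight will be measured once 2 weeks, 4 weeks and 3 months after discharge". Length and head circumference follow the same timing.

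**The concern.** A no-effect aim needs a statement of how large an effect would still count as none. A comparison of group means without that statement can show a difference, but it cannot show the absence of one. The less precise the growth data, the more likely a non-significant result, whatever the truth.

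Growth is this trial's nutritional-safety question. Table 1 gives 66 versus 80 kcal and 1.6 versus 2.6 g protein per 100 ml for EHF and the preterm formula. The Background puts the EHF protein-to-energy ratio below a European recommendation and reports conflicting findings on whether such formula meets the needs of preterm children. The Discussion itself says that the question is unsettled. A conclusion of no effect on growth could influence feeding practice, so the plan should say what evidence would justify it.

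**Working it through.** **Inputs.** Evaluable infants per arm: 148, at the end of the NICU part (Sample size justification). Growth reference: 15 g/kg/d weight gain (Background). Two-sided 5 % test (assumed for growth, since no level is stated). SD of growth: not given, so results are shown first in SD units and then for an assumed SD of 3, 4 or 5 g/kg/d.

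**The plan's own figure.** There is none for growth. The step from 148 to 185 enrolled reproduces: 148/0.80 = 185. The 148 itself does not follow from 85 % versus 75 % at 80 % power, because the usual two-sided formula gives 250 per arm. That is a separate matter, and 148 is used here only as the planned size.

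**Step 1, precision.** SE = SD × √(2/148) = 0.116 SD. The 95 % CI half-width is 1.96 × 0.116 = 0.23 SD. The deficit detectable with 80 % power is (1.96 + 0.84) × 0.116 = 0.33 SD.

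**Step 2, chance that a real deficit is non-significant.** This is 1 − Φ(deficit/SE − 1.96).

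| True deficit | Deficit/SE | Non-significant |
|---|---|---|
| 0.20 SD | 1.72 | 59 % |
| 0.25 SD | 2.15 | 42 % |
| 0.30 SD | 2.58 | 27 % |

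**Step 3, in weight-gain units (assumed SD, deficit 1 g/kg/d).**

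| SD (g/kg/d) | SE | 1/SE | Missed |
|---|---|---|---|
| 3 | 0.349 | 2.87 | 18 % |
| 4 | 0.465 | 2.15 | 42 % |
| 5 | 0.581 | 1.72 | 59 % |

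**Step 4, after discharge.** The 148 applies to the end of the NICU part. If a further 20 % were lost by 3 months (assumption), 148 × 0.80 ≈ 118 per arm would remain. The three probabilities in Step 2 would then rise to 66 %, 52 % and 37 %.

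**Step 5, whether a margin is workable.** With one-sided 2.5 %, 80 % power and a true difference of zero, the non-inferiority size per arm is 2 × (1.96 + 0.84)² / (margin in SD)². This gives 252 for 0.25 SD, 175 for 0.30 SD, 145 for 0.33 SD and 99 for 0.40 SD. The planned 148 therefore supports a margin of about 0.33 SD or wider.

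An illustration, not a proposal: take a margin of 1.5 g/kg/d, which is 10 % of the 15 g/kg/d reference. Power at a true difference of zero is Φ(1.5/SE − 1.96) = 99 %, 90 % and 73 % for SD 3, 4 and 5. The same margin would accept a true deficit of 1 g/kg/d with probability Φ(0.5/SE − 1.96) = 30 %, 19 % and 14 %. The choice of margin therefore matters and needs clinical justification.

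**Step 6, size of the nutritional contrast.** This is an equal-volume scenario only. At 150 ml/kg/d, energy is 1.5 × 66 = 99 versus 1.5 × 80 = 120 kcal/kg/d, and protein is 1.5 × 1.6 = 2.4 versus 1.5 × 2.6 = 3.9 g/kg/d. At equal energy, say 110 kcal/kg/d, the energy gap vanishes and protein is 110 × 1.6/66 = 2.7 versus 110 × 2.6/80 = 3.6 g/kg/d.

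**The case against.** The strongest reply has four parts.

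First, a reader might infer that a non-significant growth result will be reported as proof of no harm. No sentence says so. The p < 0.05 rule is attached to the primary outcome only, and both the Abstract and the Background pose the growth question openly. This stands, so the point is limited to what the planned analysis could support. It does not extend to what the investigators will do.

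Second, ANCOVA is not a wrong method, and a margin or CI rule may be in an analysis plan that is not shown. The first half stands: the model yields the estimate and interval that are needed. The second half is only partly an answer. The article itself sets the no-effect aim, names the model and announces the conclusion, and those statements need a criterion or softer wording in any case.

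Third, the SD is assumed, and a two-mean formula ignores covariate adjustment and repeated measures, which usually reduce the SE. This is fair. The SD can be read as the residual SD after adjustment, and the SD-unit results then hold approximately. A smaller residual SD moves the g/kg/d figures towards the favorable end.

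Fourth, two further readings are tempting. One is that discharge-timed visits bias the growth comparison by a known amount. The endpoints are growth rates rather than attained size, the time axis of the model is not stated, and discharge requires a corrected age of at least 34 weeks. No size can therefore be put on such a bias. The other is that EHF infants will receive 21 kcal/kg/d less. That assumes equal volumes at the discharge minimum, whereas the article defines full enteral nutrition by energy, at 100–120 kcal/kg/d. Neither reading is supported.

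**Conclusion.** The concern holds as a mismatch between claim and analysis. The aim and the announced conclusion are of no effect on growth, while the stated analysis compares groups without a margin or CI criterion. At 148 per arm, deficits of 0.20 to 0.30 SD would be non-significant about 59 % to 27 % of the time, given a two-sided 5 % test and equal arms. The range of 18 % to 59 % for a 1 g/kg/d deficit also rests on the assumed SD of 3 to 5 g/kg/d.

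This does not show that EHF slows growth, nor that the trial will misreport a null result. It shows that a null result would leave the no-effect statement unsupported. The timing of visits is a minor supporting point: length of NICU stay is itself an endpoint that EHF is hoped to shorten, so the arms may differ in age at a given visit. The change should be made, but the primary analysis is not affected.

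**What to change.** Keep the ANCOVA. Before the growth data are seen:

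1. Name the key growth-rate measure and period, for example daily weight gain during the NICU stay.
2. Set a non-inferiority margin for it. Its size is a clinical choice for the sponsor to justify.
3. State that a no-effect claim on growth will be made only if the 95 % CI of the EHF-minus-control difference excludes that margin. Otherwise, report the estimate and CI without the claim.
4. If no margin can be justified, reword the Secondary objective and the last sentence of the Discussion as estimation: whether EHF changes growth, and by how much.
5. In the post-discharge growth model, include age at measurement (postmenstrual or postnatal), gestational age and birth size.

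The cost is some wording and one justified margin. Data, visits and model family are unchanged. The downside is that the no-harm claim may not be met, particularly if the margin is narrower than about 0.33 SD or many infants are lost by 3 months.
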